### Intervention

#### Overview

The intervention was delivered using a VR-HMD worn by the older adults—a Pico Neo 3 Pro (Pico Interactive) in the experimental group and a Pico G2 in the control group. The content shown in the VR-HMD consists of 2 key components.

#### Base Content

The base consent comprises high-quality 360° photographs and videos from natural environments in the real world, such as a relaxing environment with a mountain view. Initially, 80 different base content environments were used.

#### Graphical Overlay

##### Overview

The base content has a graphical overlay that has 2 key components.

##### Hands

The user’s hands and their position are shown inside the VR environment as virtual hands, moving in real time. This requires the user to hold a controller in each hand. The user’s hands and their positions are displayed within the VR environment as digital hands that move in real time. This setup requires the user to hold a controller in each hand.

##### Graphical Objects

Graphical objects are, for example, balloons, that users can touch using their virtual hands. These appear inside the VR environment and move in prespecified trajectories. Graphical objects, such as balloons, can be touched by users through their digital hands. These objects appear in the VR environment and follow predetermined trajectories. The intentions of this design were (1) to perform physical exercises (moving the arms and upper body to touch the graphical objects) and (2) to perform cognitive exercises (using the arms to touch graphical objects according to specific rules for each cognitive task).

While performing the physical and cognitive exercises, the participants could also listen to a selection of musical pieces from the HealthTunes database. The music was played in stereo (48 kHz 24-bit WAV files, –15 dB LUFS) on the Pico G2 and Pico Neo 3 Pro VR-HMDs. All tracks were organized by HealthTunes [27]; none had any drastic tempo changes that could adversely entrain participants or any drastic dynamic changes that could interfere with the experience. The levels of the audio frequency bands were also adjusted to optimize the music to the older adults’ hearing. The selection of musical pieces is presented in Multimedia Appendix 2. Participants were provided with a choice of music spanning 4 genres—classical, ambient, electronic, and jazz, with the option to select rock music. This diverse selection was intended to accommodate individual preferences and enhance the personalization of the VR experience. Classical music was the most popular choice among participants, featuring a variety of operas and symphonies or concerti from renowned composers, offering a rich tapestry of auditory stimuli conducive to cognitive stimulation and relaxation. The cognitive exercises that were implemented within the VR app are as follows:

Warm-up: a simple exercise to familiarize the participant with each task, in which participants must select the graphical objects that match the color of their hands. The warm-up introduction is presented in Figure 1 and a warm-up exercise is presented in Figure 2.Focus: an exercise of focused attention in which participants must select the graphical objects that match the color of their hands and avoid those that do not. The focus introduction is presented in Figure 3 and a focus exercise is presented in Figure 4.Switch: an exercise for alternating attention in which participants must reach alternately for the shapes of the graphical objects with the matching hand color. The switch introduction is presented in Figure 5 and a switch exercise is presented in Figure 6.Memory: an exercise of working memory based on the n-back task, in which participants must tap a graphical object if it is the same color as the one that appeared 2 graphical objects earlier. The memory introduction is presented in Figure 7 and the memory exercise is presented in Figure 8.

**Figure 1 figure1:**
[figure not shown]
Warm-up introduction.

**Figure 2 figure2:**
[figure not shown]
Warm-up exercise.

**Figure 3 figure3:**
[figure not shown]
Focus introduction.

**Figure 4 figure4:**
[figure not shown]
Focus exercise.

**Figure 5 figure5:**
[figure not shown]
Switch introduction.

**Figure 6 figure6:**
[figure not shown]
Switch exercise.

**Figure 7 figure7:**
[figure not shown]
Memory introduction.

**Figure 8 figure8:**
[figure not shown]
Memory exercise.

The targeted sample size was 200 participants, equally divided between the experimental and the control groups. Both groups were balanced regarding sex.

The experimental group members underwent a 3-month computerized VR dual-task training program, as described. The control group passively experienced 360° photographs and videos from natural environments without dual-task physical and cognitive training. This technique is frequently used in cognitive studies, offering a passive experience devoid of cognitive challenges [28]. In both groups, the participants were encouraged to use the VR-HMD for a minimum of 3 sessions of 12 minutes per week for 3 months, that is, for at least 36 sessions in total.

The first training session occurred at the MUL, where the participants were trained on how to use the VR-HMD. At the end of the session, the participants took the VR-HMD to their homes to use them according to the schedule described.

The adverse effects of using VR headsets, often referred to as cybersickness, have been reported to include eye strain, dizziness, nausea, and vomiting [29]. However, these side effects are most often due to suboptimal use of the technology, for example, by using VR content with quick changes of position, low image resolution, and low display refresh rates. The VR app used in the study was designed specifically for older adults and avoided any such drastic camera movements.

The app used in the control group had previously been tested by older adults in 15 older adult care homes in Switzerland and Finland. The first version of the app, containing cognitive training, used in the experimental group was tested by 30 older adults in usability studies by terzStiftung in Switzerland between September 2021 and January 2022. After 8 workshops, the feedback was used to develop updated versions of the app. The resulting cognitive training program, image quality, and usability were rated as high by the participants [30]. The results confirm that VR-HMDs are safe for use by high-functioning healthy older adults at home without substantial risks or side effects.

Nevertheless, participants received explicit instructions to discontinue the VR intervention and contact the researchers if they experienced any side effects. Moreover, in the case of suspected side effects, the participants would be withdrawn from the study, and this would be reported as an adverse event. Any side effects could be reported through a software app running on their mobile phone, tablet, or computer. At the end of the intervention, an open-ended questionnaire was used to collect feedback, including information on perceived side effects.

To acquire reliable and comprehensive outcome data, strategies were used to promote participant retention and ensure follow-up completion (Textbox 2). If participants discontinued the intervention or deviated from the protocol, information regarding their decision was collected with various self-reported outcome data related to their experience, expectations, perceived benefits, and any changes observed during their participation.

Promoting participant retention and ensuring follow-up completion.

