**Supportive staff**
A dedicated research team that is easily accessible to participants will be established. Staff members will be trained to provide emotional support and address participants’ questions or concerns during the study.

Compliance and performance were monitored through a web-based platform. The researchers contacted participants who did not perform the VR training at least 3 times per week to check whether they faced difficulties using the VR app or wished to discontinue participation. Throughout the intervention, the participants were expected to avoid participating in any other trials, especially those related to cognitive functions or mental states. The participants were covered by health insurance throughout their participation in the study, concerning any potential harm, according to a standard clinical study insurance policy.

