### Conclusions

Previous research found that VR therapy can improve the well-being of older adults in long-term care, rehabilitation hospitals, and older adult care residences, who often experience cognitive decline, reduced mobility, and isolation [22]. We intend to publish our findings in a future study, and we believe that they will provide further information on the effect of immersive VR therapy among healthy, community-dwelling older adults regarding their cognitive performance, tolerance, and technology acceptance. Even so, further research is needed to explore the long-term effects, optimal intervention designs, and specific populations that may benefit most from VR-based interventions.

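### Side effects are gathered mainly by volunteered reports and one open-ended form at the end, which cannot give a reliable incidence, severity or between-arm comparison for the tolerance information the article expects

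*Protocol article*

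**What the plan says.** All references are to the protocol article.

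- **Expected harms.** The Intervention section describes the adverse effects of headsets as "often referred to as cybersickness, have been reported to include eye strain, dizziness, nausea, and vomiting". Potential Risks and Challenges adds disorientation, and Limitations adds headache.
- **During the intervention.** Two volunteered routes are described: "participants received explicit instructions to discontinue the VR intervention and contact the researchers if they experienced any side effects", and "Any side effects could be reported through a software app running on their mobile phone, tablet, or computer".
- **Consequence of a report.** "in the case of suspected side effects, the participants would be withdrawn from the study, and this would be reported as an adverse event".
- **At the end.** "At the end of the intervention, an open-ended questionnaire was used to collect feedback, including information on perceived side effects".
- **Discontinuers.** "If participants discontinued the intervention or deviated from the protocol, information regarding their decision was collected with various self-reported outcome data".
- **Low users.** After Textbox 2, the article says that researchers contacted participants who trained fewer than three times a week, "to check whether they faced difficulties using the VR app or wished to discontinue participation".
- **Outcomes.** Neither the list in Outcome Measures nor the amended primary and secondary outcomes in Challenges includes tolerance, cybersickness or technology acceptance.
- **What is expected of the findings.** The Discussion (Conclusions) says they will add information on VR therapy "regarding their cognitive performance, tolerance, and technology acceptance".

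**The concern.** The article names the symptoms it expects, but describes no point at which every participant is asked about each of them. The one planned query is free text, covers side effects as part of general feedback, and comes after about three months and at least 36 home sessions. No pre-intervention answer is described for comparison. Dizziness and eye strain can occur at ages 65 to 85 without a headset, so an answer after use cannot by itself separate background symptoms from those due to VR.

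A low count could then be read as good tolerability when it may partly reflect how the question was asked. A comparison between arms would be open to the same doubt. It would be of interest here, because the arms used different headset models and the article itself links side effects to image resolution and refresh rate.

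**Working it through.** The plan states no rate, power or sample size for tolerance, so there is no figure to reproduce. The check sets the routes side by side and then uses the counts in Participant Flow.

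**1. What each described route can give**

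| Route | Who starts it | Asks about named symptoms? | Reaches everyone? |
|---|---|---|---|
| Contacting the researchers | Participant | No, volunteered | No |
| App report | Participant | No list described | No |
| Low-use contact | Researcher | Described as app difficulties or wish to stop | Low users only |
| Information at discontinuation | Not stated | Described as the decision and experience | Discontinuers and deviators only |
| End questionnaire | Study | Open-ended, within general feedback | Not stated |

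No row is a structured symptom query put to all participants, and none is described at baseline.

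**2. Who would be asked at the end**

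- Experimental: 100 − 20 = 80 left to start; 68 completed (68/80 = 85%).
- Control: 88 − 22 = 66 left to start; 62 completed (62/66 = 94%).
- Together: 130/146 = 89% of those left to start.

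A suspected side effect leads to withdrawal. If the end questionnaire reached completers only (an assumption; the article does not say), it would mainly cover people who tolerated the headset.

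**3. What the reported flow can show**

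The counts close: 20 + 12 + 68 = 100 and 22 + 4 + 62 = 88. No withdrawal among the 146 is attributed to a side effect. Withdrawals for health problems judged unrelated were 12/80 = 15% and 4/66 = 6%. The zero may mean no side effects, no reports, or attribution to other causes. The described method cannot tell these apart.

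**4. Illustration of size**

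The symptom rates and capture shares below are assumptions, not figures from the documents.

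- Under-counting: true rate 20%, so 0.20 × 80 = 16 cases. With 25% captured, 16 × 0.25 = 4 are counted (5% of 80). With 75% captured, 16 × 0.75 = 12 (15%).
- Zero events, even with full capture: the two-sided 95% upper bound is 1 − 0.025^(1/n). For n = 68 it is 5.3%, and for n = 80 it is 4.5%.
- Power for a between-arm difference, 80 versus 66, two-sided α = 0.05: Φ[(|p₁ − p₂| − 1.96·SE₀)/SE₁], where SE₀ is the pooled and SE₁ the unpooled standard error. For 20% versus 10% with full capture, SE₀ = 0.0602 and SE₁ = 0.0580, so Φ[(0.10 − 0.118)/0.058] = Φ(−0.31) = 38%. With half captured in both arms (10% versus 5%) it is 19%, and with a quarter captured (5% versus 2.5%) it is 11%.

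Even full capture would leave a between-arm comparison weak, and incomplete capture makes it weaker.

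**The case against.** **More routes exist than the app and the final form.** A reader might infer that these two are the only sources. The text does not support that: participants were told to contact the researchers, discontinuers were asked about their decision and experience, and low users were called. This stands. None of these is described as a systematic symptom query, however.

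**No conclusion on tolerance is promised.** A reader might infer that the trial commits itself to a tolerance conclusion it cannot deliver. The Discussion expects further information, no between-arm comparison of side effects is stated, and tolerance is not in the objective, the hypotheses or the outcomes. Withdrawals, usage logs and reported events do give some information. This also stands, and limits the point to what that information can support.

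**Some supporting arguments are inference.** The article does not say that the symptoms are short-lived. It does not say that participants hold back reports; they were told to report. The withdrawal rule could give someone who wishes to continue a reason for silence, but that is a possibility only. The low-use call may have covered symptoms. Reporting procedures are described alike for all participants, so nothing shows that capture differed by arm.

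**The full protocol is not shown.** The questionnaire, app screen and call script could contain symptom prompts. This is fair. The point therefore rests on the method the article does state, on its outcome lists, and on the mismatch with its Discussion, not on missing detail.

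**Conclusion.** The point holds in a limited form. Side-effect data come mainly from volunteered reports and one late open-ended form, without a described baseline or structured query, while the Discussion expects information on a quantity that is not an outcome. These data can support a list of reported events and withdrawals. They cannot support a reliable incidence, severity or comparison between arms. Limitations discusses cybersickness for its occurrence and its effect on adherence, but not for how it was measured.

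The size cannot be fixed from the documents. The 4 to 12 counted out of 16, and the fall in power from 38% to 19% or 11%, only illustrate the assumed rates and capture shares. The selection of tolerant participants into the end questionnaire depends on the assumption that only completers received it.

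A reader might also take the 15% versus 6% of withdrawals for health problems as a sign of harm. The documents do not support that: these were recorded as unrelated. The described data simply offer no systematic symptom record against which to check the attribution.

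**What to change.** **For the design.** Replace the open-ended side-effect item with a short closed checklist of the symptoms already named in Intervention, Potential Risks and Challenges, and Limitations: eye strain, dizziness, nausea, vomiting, disorientation and headache. Record presence and severity, and keep one free-text line. Give it in the same form in both arms at the baseline visit, before the headset is first used, and at the end visit, including to discontinuers where possible. Add the same items to the existing app and the low-use call. Report by arm the symptoms that are new or worse since baseline. The withdrawal rule need not change for this.

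**Cost.** One brief form at two visits that already take place, and a few items in an existing app and call. The downside is a few minutes of participant time and a higher recorded symptom count, since a checklist elicits more reports than an open question.

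**For this completed trial.** A baseline checklist can no longer be added. Either remove tolerance from the Discussion (Conclusions), or limit it to spontaneously reported events and withdrawals. In the second case, state the ascertainment limitation next to the cybersickness paragraph in Limitations. If the full protocol contains a structured instrument, describe it instead. Any of these costs a sentence or two.

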**Clear expectations**
The study requirements, including the duration of the intervention, the frequency of sessions, and any follow-up assessments, will be communicated. A comprehensive overview of the study timeline should be provided to participants, and their continued participation should be emphasized.
**The informed consent process**
During the informed consent process, efforts will be made to ensure that participants fully understand the study’s goals, procedures, and potential benefits. Concerns expressed by participants will be addressed and their questions will be answered to foster their commitment to the study.
**Flexible scheduling**
Participants’ schedules and preferences will be considered when planning pre- and postintervention assessments. Flexibility in scheduling will be offered to accommodate their availability, facilitating the completion of the required sessions.
**Reminders and communication**
Periodic reminders about upcoming sessions or assessments will be sent to participants via SMS text messages and phone calls. Clear instructions, directions, and any necessary materials or equipment for the virtual reality –based training will be provided to participants.
**Supportive staff**
A dedicated research team that is easily accessible to participants will be established. Staff members will be trained to provide emotional support and address participants’ questions or concerns during the study.

Compliance and performance were monitored through a web-based platform. The researchers contacted participants who did not perform the VR training at least 3 times per week to check whether they faced difficulties using the VR app or wished to discontinue participation. Throughout the intervention, the participants were expected to avoid participating in any other trials, especially those related to cognitive functions or mental states. The participants were covered by health insurance throughout their participation in the study, concerning any potential harm, according to a standard clinical study insurance policy.

### Outcome Measures

Neuropsychological assessment was performed at baseline and after the intervention. The primary outcomes of the initial study comprised the cognitive, social, and physical performance abilities of healthy (high-functioning) older adults. The parameters that were selected are (1) a wide range of cognitive domains: composite memory, verbal memory, visual memory, psychomotor speed, reaction time, complex attention, cognitive flexibility, processing speed, executive function, simple attention, and motor speed (Central Nervous System Vital Signs [CNS-VS] battery) [31]; (2) physical performance across 6 subcomponents: lower body strength, upper body strength, aerobic endurance, lower body flexibility, upper body flexibility, and dynamic balance or agility (Senior Fitness Test); (3) standard grip strength (using a dynamometer); (4) the sense of loneliness (De Jong Gierveld Loneliness Short Form); (5) the quality of life and perceived well-being (World Health Organization [WHO]–5 Well-Being Index); (6) the health-related quality of life (EQ-5D-5L); (7) satisfaction with participation in social roles and ability to participate in social roles and activities (Patient-Reported Outcomes Measurement Information System Short Form 8a); and (8) the severity of anxiety symptoms (General Anxiety Disorder 7-item questionnaire [GAD-7]) [32].

The CNS-VS is a computerized neurocognitive test battery developed as a routine clinical screening instrument. It comprises 7 tests—verbal and visual memory, finger tapping, symbol digit coding, the Stroop Test, a test of shifting attention, and the continuous performance test. The result includes neurocognitive clinical evaluation domains—composite memory, verbal memory, visual memory, psychomotor speed, reaction time, complex attention, cognitive flexibility, processing speed, executive function, simple attention, and motor speed [31]. The CNS-VS clinical battery is sensitive to subtle cognitive deficits and progressive decline or improvement. Previous research has shown it is validated, reliable, and easy to use [33].

The WHO-5 Well-Being Index is a 5-item measure of well-being with high internal consistency, evidence of a 1D factor structure, and high convergent associations with other measures of well-being [34,35]. The respondent is asked about their well-being in the last 14 days. Each of the 5 items is scored from 5 (all of the time) to 0 (none of the time). The raw score ranges from 0 (absence of well-being) to 25 (maximal well-being) [36].

The EQ-5D-5L is a questionnaire used to assess health-related quality of life. It measures the problems experienced in 5 domains, which are, mobility, self-care, usual activities, pain or discomfort, and anxiety or depression. The questionnaire also includes an overall health scale where individuals rate their health condition from 1 to 100, with 100 representing the best imaginable health. Previous research has found the EQ-5D-5L to be reliable and valid [37].

The GAD-7 was used to measure the severity of anxiety symptoms. Each item considers different anxiety symptoms and is answered on a 4-point Likert-like scale. The total score ranges from 0 to 21, and a rise in the score indicates more severe anxiety. The tool is sensitive to anxiety in nonclinical samples and to changes in the severity of anxiety symptoms.

Grip strength was assessed with a hand-held dynamometer. The method is a reliable measure of the strength of muscles in older adults when using a standardized protocol and instructions [38]. The resulting grip strength data have been reported to predict general muscle strength and physical functioning in the older adult population [39,40].

